### Outcomes Measures

The outcome for each model will be the occurrence of NODAP. For reference, new-onset diabetes after organ transplantation mainly occurs 3–6 months after the operation, and the incidence drops to 4–6% 1 year after the operation (30). The onset of NODAP mainly occur within 1 year after the operation, thus the follow-up time of outpatient was determined to be no less than 12 months.

### Statistical Analysis

Baseline demographic characteristics and study outcomes conforming to normal distribution were expressed as mean ± standard deviation. The *t*-test was used for comparison between the two groups. The measurement data not conforming to normal distribution was represented as the median (quaternary interval), and the comparison between the two groups was performed using the Mann–Whitney *U* test. Descriptive statistics will be used for the overall cohort and aggregated statistics will be calculated. Descriptive statistics are used for the entire queue and the aggregated statistics are calculated. Enumeration data were expressed as frequency or percentage, and χ*2* test was used for comparison between the two groups. Univariate analysis was conducted for all factors first, and statistical learning methods such as tree integration algorithm and Lasso regression were adopted to compare and screen related risk factors from multi-dimensional perspectives. To avoid omission of important variables, covariates with *P* < 0.01 in univariate analysis and important factors screened by statistical learning method were included in multivariate logistic regression analysis. Independent risk factors for NODAP were analyzed by progressive forward regression analysis, and the OR value of each related factor and its 95%CI were estimated. *P* < 0.05 on both sides of all tests indicated statistically significant differences.

We will evaluate the potential predictors of NODAP informed by prior literature (10, 20). The data set will be randomly divided into a training dataset and an internal validation dataset in a 5:5 ratio. We will include all a priori selected variables in the final model; the Bootstrap method was used for model internal validation in this data set. If necessary, non-normally distributed variables will be transformed using the Box-Cox transformation. The validation will be established with the same inclusion and exclusion criteria and sensitivity analyses will be performed. All analyses were performed using R3.6.1 and SPSS^®^ Statistics 21 software (IBM^®^, Armonk, NY, USA). Prism 5 (GraphPad Software Inc., San Diego, CA, USA) is used for drawing statistical graphs.

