## Introduction

Type 2 Diabetes mellitus (T2DM) is a major health concern worldwide, with a prevalence of about 463 million by 2019, and a 62% increase since 2009 (1). In Chinese adults, the estimated T2DM and pre-T2DM prevalence are 10.9% and 35.7% (2), respectively. It is a strong risk factor for cardiovascular artery disease (CAD) and major adverse cardiovascular events (MACE) (3–5). A pooled analysis involving more than 1 million participants in Asia found that patients with T2DM had a higher risk (hazard ratio, 1.89) of all-cause death than those without T2DM (6). People are conferred an eight fold increase in death risk by unrecognized myocardial infarction (MI) with diabetes (7). As patients with acute ST-segment elevation myocardial infarction (STEMI) significantly improved after percutaneous coronary intervention (PCI), the 10-year survival rate was nearly 76% (8). Prolonged life expectancy makes chronic care management after PCI a concern. Nearly half of the inpatients with MI complicated with T2DM (9, 10) and good blood glucose control is one of the keys. There have been multiple studies regarding clinical outcomes in patients after PCI with known T2DM (11, 12). Patients after PCI with chronic T2DM emerge with poor clinical outcomes and different treatment strategies (13, 14). Patients approximately 30% who underwent PCI suffer from diabetes (13). Considering the counter-balancing effects of hemorrhagic and ischemic complications, the recent ultra-short DAPT strategy may not be suitable for patients with T2DM (15). New-onset of diabetes after PCI (NODAP) has attracted much attention; a 5-year survival of patients after revascularization with diabetes were worse (16). Among 3,683 acute coronary syndrome (ACS) patients (without T2DM before PCI), 436 patients (11.8%) developed NODAP after a follow-up of 3.41 ± .9 years (10).

However, the risk factors and pathophysiological mechanisms for NODAP remain unknown. The risk factors for NODAP may be different from those for simple diabetes. Patients after PCI are generally elderly, and are associated with a variety of metabolic diseases (obesity, hyperlipidemia, etc.) and stress states related to surgery; all the above predict the risk of T2DM. Previous studies show that abnormal heart rate variability is a risk factor for diabetes (17), and heart rate variability (low SDNN) is common in patients undergoing PCI (18). High intensity statins (19, 20) also has adverse effects on diabetes.

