**Inclusion criteria**	
i	Age > 18 years
ii	Adults with a primary diagnosis of an ACS (23)
iii	Did not meet the diagnostic criteria for diabetes (24, 25) before the PCI surgery^*^, no history of taking hypoglycemic drugs or insulin
iv	Only have received the initial PCI
v	outpatient follow-up ≥12 months
vi	Volunteer to participate in the study

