### Data

The data extracted from the hospital information system (HIS) will exclude the privacy of participants; detailed parameters will vary based on each institution, which may include outpatient and inpatient medical history and diagnostic imaging database. To ensure the unified management of mass data among multiple institutions, we have established a third-party data management platform (*http://121.30.232.162:10094/#/user/login?redirect=%2F*). Every participant will be assigned a systemic number separate from the medical record number. Based on the platform, the required information can be retrieved and excluded. After machine retrieval by a third-party platform, two researchers will review each participant for inclusion in the study.

Using data provided from decision support at four hospital sites, we expect at least eligible patients in the period 2010–2021, and data according to the fields included in the diagnosis (acute coronary syndrome, PCI, diabetes, etc.) and CCCDNCE 2.0 codes. A standardized case report form (CRF) that has been pilot tested and refined will be used for data extraction. Trained researchers will enter the identified data directly using the electronic CRF into the online platform managed in Beijing, China.

Data will be collected with traditional Chinese and western medicine characteristics that are important in the management of ACS patients with NODAP to confirm the baseline level and severity of blood stasis syndrome. Data will be included in two stages. First, ACS patients who were eligible for inclusion criteria were included. All these patients will be re-screened to ensure the duration of 12 months of follow-up and above. Structural data such as demographic information, diagnostic testing and medication situation can be directly collected in the database. Medical history and surgery records will be retained in the platform in unstructured text format. Researchers in charge of each institution will ensure consistency on extraction method and content, and train individuals for data identification and extraction, and entering DE identified data using the electronic CRF. Relevant medical history including history of ACS, history of T2DM, history of PCI surgery will be collected to confirm the diagnosis. New-onset diabetes was diagnosed by fasting blood glucose or HbA_1_c levels in the outpatient or inpatient biochemical test during follow-up.

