### Limitations

This study has some limitations. As the study is a non-randomized retrospective study, selection bias cannot be excluded. Based on diagnosis name or CCCDNCE 2.0 codes, eligible patients may miss some medical records that would have met eligibility criteria, including those that were given a broader diagnosis or incorrect ICD code. However, given a large number of sites and patients identified with decision support, we anticipated that only a small number of patients will be omitted. Given its retrospective design, included data will be limited by what is documented in the HIS, thus some of the data we are interested in cannot be obtained (e.g., waistline). Third, as an observational study, we were only able to address association rather than causation, if any predictors are identified with surgical outcome, education levels, or income levels. However, the analyses outlined are exploratory in nature. Fourth, given the 12-month follow-up period, it is not enough for all patients at risk to develop NODAP, which may act as unmeasured confounders.

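### New-onset diabetes is modelled as yes/no by logistic regression over follow-up with a 12-month floor and no horizon, so predicted risks have no time frame and some odds ratios can reflect length of observation

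*Protocol article*

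**What the plan says.** All references are to the protocol article.

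- **Outcome.** Outcomes Measures: "The outcome for each model will be the occurrence of NODAP". The Data section gives the ascertainment: "New-onset diabetes was diagnosed by fasting blood glucose or HbA_1_c levels in the outpatient or inpatient biochemical test during follow-up". Neither sets an end point in time.
- **Follow-up.** Table 1, inclusion criterion v: "outpatient follow-up ≥12 months". The Data section (re-screening step) and Outcomes Measures also treat 12 months as a minimum. Records come from 2010–2021. A longest follow-up of about 11 years is inferred from that span; the article states no maximum.
- **Model.** Statistical Analysis: "important factors screened by statistical learning method were included in multivariate logistic regression analysis", and "the OR value of each related factor and its 95%CI were estimated". The univariate entry rule is P < 0.01. Model Evaluation compares models by the area under an ordinary ROC curve.
- **Candidate variables.** Table 2 lists neither length of follow-up nor calendar year, and no dates. No censoring, person-time or time-to-event method is named.
- **Timing of onset.** Outcomes Measures: "The onset of NODAP mainly occur within 1 year after the operation". Limitations: "given the 12-month follow-up period, it is not enough for all patients at risk to develop NODAP", which the section then describes as a possible source of unmeasured confounding. The Introduction cites a cohort in which 436 of 3,683 patients "developed NODAP after a follow-up of 3.41 ± .9 years".

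**The concern.** Under these rules a patient free of diabetes after 12 months and one free of diabetes after about 11 years carry the same code, although the second had far more time in which to be diagnosed. Two things follow.

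First, the aim is a prognostic tool. A logistic model fitted to such data returns a probability averaged over whatever follow-up lengths the sample contains. It is not a risk by 1 year or by 5 years, so it cannot be applied to a new patient. The random 5:5 split does not reveal this, because both halves share the same mixture.

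Second, a predictor that is more common among patients followed for longer, or for less time, takes on part of the effect of observation time. That can influence variable screening, the reported odds ratios and the AUC ranking of models.

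This is not a detail left to an unseen analysis plan. The article itself fixes the open-ended outcome, the floor-only follow-up and the logistic model.

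**Working it through.** **Inputs.** From the Introduction: 436 events in 3,683 patients, mean follow-up 3.41 years. From Table 1: minimum follow-up 1 year. From the record period: maximum about 11 years (inferred). From Sample Size: expected NODAP proportion 6.1–11.6%. The shape of the hazard, the distribution of follow-up and the predictor's prevalence are assumptions, so each result is shown as a range.

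**The plan's own figures.** 436/3,683 = 0.118, the quoted 11.8%. Sample Size: 10,000 × 0.061 = 610, as stated.

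**Step 1: risk at different horizons for the same patient.**
Cumulative hazard at 3.41 years: H = −ln(1 − 0.1184) = 0.1260.
If a fraction f of H falls in year 1, then for t ≥ 1:
risk(t) = 1 − exp{−[fH + (1 − f)H(t − 1)/2.41]}.
Constant hazard is f = 1/3.41, or 0.1260/3.41 = 0.0369 per year.

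| Share of H in year 1 | Risk at 1 year | Risk at 11 years | Odds ratio, 11 vs 1 year |
|---|---|---|---|
| 29% (constant hazard) | 3.6% | 33.4% | 13.3 |
| 50% | 6.1% | 27.7% | 5.9 |
| 75% | 9.0% | 20.2% | 2.5 |
| 90% | 10.7% | 15.3% | 1.5 |

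Example, constant hazard: (0.334/0.666)/(0.0363/0.9637) = 13.3. Example, 90%: (0.1527/0.8473)/(0.1072/0.8928) = 1.5. These odds ratios come from observation time alone.

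**Step 2: a predictor with no effect on the hazard (simulation).** Prevalence rises linearly from 20% in patients with the earliest PCI (longest potential follow-up) to 60% in those with the latest.

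- *Uniform 1–11-year follow-up.* Odds ratio 0.77 under constant hazard, and 0.81, 0.88 and 0.95 with 50%, 75% and 90% of H in year 1. At constant hazard, P < 0.01 occurs in about 84% of samples of 5,000; at 90% in year 1, in about 2.5%.
- *Drop-out added so that overall incidence is about 11%.* Odds ratio about 0.89 under constant hazard to about 0.98 with 90% in year 1. At constant hazard, P < 0.01 occurs in about 12% of samples of 5,000.
- *Predictor unrelated to follow-up.* Odds ratio about 1.0 for every hazard shape.

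**Step 3: discrimination.** With uniform 1–11-year follow-up, length of follow-up alone gives an AUC of about 0.66 (constant hazard), 0.63 (50% in year 1) and 0.54 (90%).

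**The case against.** The strongest case on the other side has four parts.

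1. **The large figures need favourable assumptions.** Constant hazard with uniform 1–11-year follow-up implies 19.4% overall NODAP, against the 6.1–11.6% the protocol expects, and it sets aside the statement that onset falls mainly in the first year. Samples of 5,000 are also an assumption: Sample Size calculates 300 per set, without saying whether these are patients or events. This stands. The roughly ninefold spread in risk and the odds ratio of 0.77 are the upper end of a range, not an expected size.
2. **Not every odds ratio is affected.** A reader might infer that all of them are distorted. The calculation does not support that: a predictor unrelated to follow-up is not pulled away from 1.0. Nor does the article document a calendar trend in statin intensity, stent length or HbA1c testing; such trends are plausible examples only. A change in testing frequency would also be an ascertainment problem that a time-to-event model does not remove.
3. **The article does not flatly contradict itself.** A reader might set Limitations against Outcomes Measures. That 12 months is too short for all patients at risk is compatible with onset being mainly within 1 year, and 11.8% over 3.41 years says nothing about timing within that period. What remains is that unmeasured confounding is the wrong name for unequal time at risk.
4. **The limitation is disclosed and the analyses are called exploratory.** True, but disclosure does not give the predicted risk a horizon.

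The reference in Limitations to a 12-month follow-up period might suggest a fixed window. Table 1, Data and Outcomes Measures all make it a minimum.

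**Conclusion.** The point holds in this form. As written, the model produces risks with no time frame. That follows from the outcome definition and the open-ended follow-up, and needs no assumption about the hazard beyond new cases continuing after the first year. Odds ratios are open to bias only for predictors related to length of follow-up.

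The size cannot be fixed from the article. For a strong 20%-to-60% prevalence shift, a null odds ratio lies between about 0.77 and 0.98, and the values nearer 1 go with the protocol's own incidence or with early onset. The stronger readings, that the odds ratios are generally spurious or that null predictors would routinely pass the screen, are not supported. The defect should still be corrected before analysis, because it reaches the outcome on which every model is fitted and compared, and correction is cheap.

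**What to change.** In Outcomes Measures, Statistical Analysis and Model Evaluation, declare a prediction horizon and choose one of two routes.

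- **(a) Fixed horizon.** Define the outcome as NODAP within 12 months of the index PCI. Every included patient has the required follow-up, so the logistic, machine-learning and ROC plan can stay, with odds ratios and risks labelled as 12-month quantities.
- **(b) Time to event.** Define the outcome as time from the index PCI to first qualifying NODAP, with censoring (for example a Cox model), and report risk and AUC at a stated horizon.

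In Limitations, replace the reference to unmeasured confounders with unequal time at risk.

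**Cost.** Mostly wording and modest programming, but PCI, test and last-visit dates must be extracted, because Table 2 does not list them. Route (a) discards later events. Route (b) knows the time of diagnosis only to the nearest test. Criterion v also means that the cohort is conditioned on surviving and attending for the first year. This matters particularly for (b), where first-year time at risk is guaranteed by design, and it should be stated.

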We propose leveraging advancements in machine learning by systematically comparing different modeling approaches (21), to develop a prognostic tool for NODAP. Therefore, we put forward the following hypothesis:

Refer to common risk factors such as obesity and smoking and explore the risk factors for NODAP; probing the risk of NODAP in different types of ACS patients (STEMI, NSTEMI, and UA) is equal or not.Systematically apply several machine learning algorithms to establish a predictive model of NODAP and verify its effectiveness.In this study, we sought to investigate the potential predictors of ACS patients with NODAP and comparatively evaluate performances of these predictive models with each other, to identify which is the most accurate.

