### Model Evaluation

Model evaluation will be carried out quantitatively via receiver operator characteristic (ROC) analysis (34). ROC curves will be constructed to evaluate and compare the predictive models. A ROC curve plots sensitivity and specificity at a range of threshold settings. The area under the curve provides an aggregate measure of model performance across all classification thresholds and will be used to compare predictive models.

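### The second aim promises a comparison of several machine-learning prediction models, but the model-building text gives tree and Lasso methods the role of screening variables for a logistic regression

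*Protocol article*

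**What the plan says.** **The aim.** The Introduction proposes "leveraging advancements in machine learning by systematically comparing different modeling approaches". Its second hypothesis is to "Systematically apply several machine learning algorithms to establish a predictive model of NODAP and verify its effectiveness", and it then undertakes to "comparatively evaluate performances of these predictive models with each other, to identify which is the most accurate". Outcomes Measures refers to the outcome of each model, in the plural sense. Model Evaluation states that "ROC curves will be constructed to evaluate and compare the predictive models" and names the area under the curve as the measure for doing so.

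**The method.** In the first paragraph of Statistical Analysis, "statistical learning methods such as tree integration algorithm and Lasso regression were adopted to compare and screen related risk factors". Covariates with P < 0.01 in univariate analysis and "important factors screened by statistical learning method were included in multivariate logistic regression analysis". Then "Independent risk factors for NODAP were analyzed by progressive forward regression analysis", with odds ratios and 95% confidence intervals as output. The second paragraph turns to literature-informed predictors, the 5:5 split and bootstrap validation, and says: "We will include all a priori selected variables in the final model". The study-design section likewise describes machine learning as leading to one prediction model.

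**The concern.** A comparison of modelling approaches needs at least two complete models, each giving a predicted risk for every patient in a common evaluation set. The aim sets up that comparison. The model-building text describes something else: the algorithms rank or select variables, and a regression is fitted afterwards.

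Two things are at stake. First, an analyst who follows Statistical Analysis as written has no instruction to score a tree ensemble or a Lasso model, so nothing specified feeds the ROC comparison that the aim depends on. Second, if those scores are produced anyway and set beside the logistic model, that logistic model has drawn part of its variable selection from the methods it is compared with. Its AUC then belongs to a two-stage procedure, and the question of which approach predicts best loses its clean answer. The records cover 2010 to 2021 and already exist, so leaving the compared models undefined also leaves room to choose them after results are seen.

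**Working it through.** The point rests on no figure in the article, so the check sets the sections side by side.

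**Step 1. What the aim needs.** The Introduction and Model Evaluation need several fitted models, each with predicted risks, compared by AUC.

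**Step 2. What Statistical Analysis specifies for each method it names.**

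| Method | Stated role | Stated as a scored predictor? |
|---|---|---|
| Tree ensemble | Compare and screen risk factors | No |
| Lasso | Compare and screen risk factors | No |
| Logistic regression | Receives the screened factors; forward selection; odds ratios | Not expressly; it is the only fitted regression described |
| Final model (singular) | Holds all a priori variables | Yes, by bootstrap internal validation; algorithm not named |

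What the first two rows compare is risk factors, not predictive accuracy.

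**Step 3. What goes into the screened logistic regression.** The candidate set, as written, is:

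candidates = {univariate P < 0.01} ∪ {factors chosen by the statistical learning methods}

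Forward selection is then applied to this union. The result is a function of the tree and Lasso selections as well as of the regression. Its AUC measures the sequence of screening, forward selection and logistic fit. It does not measure logistic regression standing alone.

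**Step 4. Whether the logistic model is itself fixed.** Forward selection can drop any candidate. The a priori rule keeps every prespecified variable. Both cannot govern the same model unless the two sets happen to coincide. Either there are two different models, which the text does not say, or there is one model with two conflicting rules.

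**Step 5. Whether another section closes the gap.** Outcomes Measures and Model Evaluation use the plural but do not say which models are meant. The study-design section uses the singular.

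**Step 6. The sizing figures.** The stated minimum of 610 events reproduces: 10,000 × 0.061 = 610. Half of it is 305, close to the stated 300 per set. The sizing works by events per predictor variable. It contains no calculation for a difference between AUCs, so it neither supports nor weakens the point.

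**The case against.** The strongest reply is that Statistical Analysis holds two analyses matching the two aims. On that reading the first paragraph, which ends in independent risk factors and odds ratios, serves the risk-factor aim. The second, with its split, bootstrap and a priori variables, serves prediction. The screened logistic regression would then never enter the ROC comparison, and the choice and tuning of the compared models would be detail that a condensed article may leave to a fuller document. The flowchart that the article points to for its method is also not available here.

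Much of this is fair. The tree and Lasso methods are introduced as examples, so the list is open. Nothing says they are used solely for screening. Both must be fitted in order to screen, so predictions could be obtained from them. The right statement is that no tree or Lasso predictions are specified, not that none can be produced.

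A reader might also infer that the pipeline guarantees a finding that logistic regression does as well as machine learning. The article does not support that. Shared candidate variables do not force equal AUCs: a tree ensemble can use interactions and non-linearity that a main-effects logistic model misses, and forward selection may remove variables that the other methods keep. Nor is screening followed by logistic regression illegitimate. It can be compared as a pipeline if it is labelled as one.

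What does not stand is the claim that this is only missing detail. The article expressly gives the named algorithms a role different from the one its aim needs. The two-analyses reading is plausible but is not stated, and under it the prediction paragraph names no machine-learning model at all.

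**Conclusion.** The point holds as a mismatch between aim and method. The comparison promised in the Introduction and Model Evaluation is not delivered by the analysis as described: of three named model types, neither tree ensemble nor Lasso is specified as a scored predictor, and the regression carries two inclusion rules. If a logistic model built on the other methods' selections were entered in the comparison, its AUC would describe a hybrid pipeline.

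No size of bias is claimed, because the article gives nothing from which to compute one. The conclusion rests on the visible text and assumes that the missing flowchart does not define the compared models differently. It should be corrected before analysis, since a declared aim depends on it and the repair is cheap.

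**What to change.** Separate the two analyses in Statistical Analysis.

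- **Risk factors.** Keep screening, forward selection and odds ratios here, and say that this analysis serves the first aim.
- **Prediction.** State that a tree ensemble, a Lasso-logistic model and an a priori logistic model are each fitted as complete prediction models from the same Table 2 candidates. Do all selection and tuning inside the training data or resample. Compare the predicted risks of all models in the same validation patients. Apply the rule of including all a priori variables to the a priori logistic model only.
- **Hybrid.** If a logistic model built on machine-learning-screened variables is also compared, label it as a hybrid pipeline and keep the a priori logistic model as the stand-alone comparator.

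Alternatively, reduce the second aim to one logistic model with machine-learning-assisted screening, state one inclusion rule, and remove the promise to identify the most accurate approach.

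The cost is revised wording and modest extra analysis work. The algorithms are already to be run for screening, and no new data are needed.

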**Patient information**	
Demographic information	age, sex, ethnicity (nationality/ethnic minorities), marital status, Occupation (physical and non-physical)
Medical history	the type of ACS (STEMI, NSTEMI, UA), smoking history, alcohol consumption history, history of hypertension, history of hyperlipidemia, history of chronic diseases, family history of T2DM, family history of CAD
Diagnostic testing	height, weight, body mass index (BMI), blood pressure, resting heart rate, fasting blood glucose, HbA1c, serum uric acid level, triglyceride level, total cholesterol level, low density lipoprotein level, left ventricular ejection fraction (LVEF)
PCI surgery-related information	number of diseased vessels, number of stent implantation, total length of the stent
Medication situation	statin medications (low intensity, high intensity), traditional Chinese medicine (Yes or No)

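### Two model-building rules stand side by side with no statement of which model each governs; the selection route leaves modest ORs uncorrected and does not guarantee an adjusted estimate for ACS type

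*Protocol article*

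**What the plan says.** All the model-building text is in the protocol article's Statistical Analysis section.

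- **First paragraph.** All factors are tested one at a time, and tree-ensemble and Lasso methods also screen them. The purpose is given as "To avoid omission of important variables". The entry rule attached to that purpose reads "covariates with *P* < 0.01 in univariate analysis and important factors screened by statistical learning method were included in multivariate logistic regression analysis". A selection step comes after it: "Independent risk factors for NODAP were analyzed by progressive forward regression analysis". For the variables that remain, the section adds that "the OR value of each related factor and its 95%CI were estimated". No entry or removal threshold is given for the forward step.
- **Second paragraph.** The data are split 5:5 into training and internal validation sets, and then "We will include all a priori selected variables in the final model". Bootstrap is named for internal validation. The predictors are said to be informed by prior literature, but no list is labelled a priori.
- **Introduction.** The first hypothesis combines exploring risk factors with "probing the risk of NODAP in different types of ACS patients (STEMI, NSTEMI, and UA) is equal or not".
- **Table 2.** ACS type is one item among 30 (5 + 8 + 12 + 3 + 2).

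**The concern.** Forward selection leaves variables out according to the data. Keeping every a priori variable forbids that. One model cannot follow both rules, and the text does not assign one rule to each of two models, so an analyst could choose after seeing the results.

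The selection route has two further effects. An estimate that must pass a significance filter on the same data is, on average, too far from 1 when the true effect is modest, and its ordinary 95% CI loses its nominal meaning. In addition, ACS type has to earn its place like any other candidate. If it drops out, the study has no adjusted comparison of STEMI, NSTEMI and UA, and its absence could be misread as evidence of equal risk. The list of independent risk factors and its ORs is a main output of the study.

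**Working it through.** **1. The plan's own figures (Sample Size section).** 10,000 × 6.1% = 610 events, as stated. Half is 305, against a stated 300 per set; the match holds if 300 means events, which the text does not say. The upper end is 15,000 × 11.6% = 1,740 events.

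**2. Chance of passing the P < 0.01 screen.** Assumptions not in the documents: one binary predictor, prevalence q = 0.20, true OR 1.3. For N patients and event rate p:

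- SE = 1/√[N·p(1−p)·q(1−q)]
- z = ln(1.3)/SE = 0.262/SE
- entry chance ≈ Φ(z − 2.576)
- mean log-OR among passers = SE × [z + φ(2.576 − z)/Φ(z − 2.576)]

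| Patients, rate | Events | SE | z | Entry chance | Mean passing OR | CI coverage given passing |
|---|---|---|---|---|---|---|
| 5,000, 6.1% | 305 | 0.148 | 1.78 | 21% | 1.59 | 88% |
| 10,000, 6.1% | 610 | 0.104 | 2.51 | 47% | 1.42 | 94.7% |
| 10,000, 11.6% | 1,160 | 0.078 | 3.36 | 78% | 1.34 | 96.8% |
| 15,000, 11.6% | 1,740 | 0.064 | 4.12 | 94% | 1.31 | 97% |

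The first row is a training half of the smallest cohort; the others are whole cohorts. At prevalence 10%, the first row's entry chance falls to 11% (z = 1.33).

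The formula is approximate. At the low end it was compared with simulations of the screen plus forward selection (20 binary candidates, 6 true with OR 1.3, about 314 to 325 events; forward threshold assumed 0.05 in the run that records one). True predictors were kept 28% to 30% of the time, with mean OR 1.53 when kept and coverage of 90% to 91%. The low-end passing OR is therefore about 1.5 to 1.6.

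**3. ACS type (2-df chi-square screen, simulated, 4,000 replicates per scenario).** Assumptions: 6.1% rate; UA 50%, NSTEMI 20%, STEMI 30%; NSTEMI log-OR half that of STEMI.

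| True STEMI-vs-UA OR | Fails P < 0.01, 5,000 patients | Fails, 10,000 patients | Mean passing OR, 5,000 | Mean passing OR, 10,000 |
|---|---|---|---|---|
| 1.2 | 91% | 81% | 1.52 | 1.37 |
| 1.3 | 80% | 54% | 1.55 | 1.40 |
| 1.5 | 43% | 8% | 1.64 | 1.52 |
| 2.0 | 1% | 0% | 2.01 | 2.00 |

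Without the filter, the mean estimates equal the true ORs to two decimals and coverage is 94% to 96%.

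**4. Room for a pre-specified model.** 305/10 = 30.5 and 305/20 = 15.25, so 305 events carry about 30 parameters at 10 events per variable, or about 15 at 20. Table 2's 30 items need about 32 parameters (ACS type counts 2, blood pressure 2). Dropping height and weight leaves about 30.

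Steps 2 and 3, apart from the simulation of screen plus forward selection, describe the univariate route only. The tree/Lasso route is not modelled because the article gives no settings for it.

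**The case against.** Several stronger readings are tempting, and the document does not support them.

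- **That the two paragraphs flatly contradict each other.** The Introduction sets two aims, risk factors and prediction. The first paragraph ends in ORs; the second turns to splitting and validation. Two models for two aims is a natural reading. It is nowhere stated, however, and the text speaks of one final model, so what stands is an unresolved ambiguity.
- **That a P < 0.01 cut is defended as a way to avoid omissions.** The phrase introduces the union of two entry routes, which admits at least as many variables as either alone. That criticism falls away.
- **That the ACS-type question may go unanswered.** Every factor is tested univariately, so a crude comparison survives. The Introduction does not promise an adjusted one, and tree/Lasso could bring ACS type in. Only the adjusted estimate is unprotected.
- **That about 21% entry is the plan's expected performance.** That figure takes the smallest cohort, lowest rate and training half. The article does not say the OR analysis is confined to the training half.

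The article also calls its analyses exploratory and limited to association, and a fuller plan may hold the variable list. Neither point says which rule applies to which model, nor corrects estimates taken after selection. The bootstrap is named for validating the model, not for adjusting ORs or intervals.

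**Conclusion.** The point holds in this form: two rules are stated without assignment, ORs and CIs after selection are uncorrected, and ACS type has no guaranteed adjusted estimate.

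The size depends strongly on inputs the article leaves open. Over its own ranges of cohort size and event rate, a predictor with OR 1.3 and prevalence 20% has anywhere from a 21% to a 94% chance of passing the univariate screen. Exaggeration is material at the low end and slight at the high end. Conditional coverage falls below 95% at the low end but slightly exceeds it at the high end, so undercoverage is not general. For ORs near 2 the bias is small. The ORs, prevalences and ACS mix are assumptions, so the percentages are illustrative. The need to settle the rule does not depend on them.

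**What to change.** State one rule per aim.

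- **Risk factors.** Fit one pre-specified logistic model on a named a priori list, without the P < 0.01 screen or forward selection, and report every OR and CI. Keep the list within the plan's events-per-variable limit: with 305 events, about 15 parameters at 20 per variable or 30 at 10. Say which figure governs. Drop height and weight, since BMI is listed.
- **ACS type.** Force it in, unpenalised, with 2 df. Report its global test and the pairwise adjusted ORs whatever the P value.
- **Prediction.** Keep tree and Lasso selection here, and repeat every selection step inside the bootstrap. Lasso should not supply the risk-factor ORs: it can drop variables and gives no standard CIs.

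The cost is wording, settled before any model is fitted. The downside is a longer risk-factor model with somewhat wider CIs. At 20 events per variable, Table 2 also has to be cut to about half on prior grounds.
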